## Aims and Hypotheses

The project has five aims:

(i)to investigate the effect of morally (in)congruent calls-to-action and salient descriptive social norms on CB;(ii)to explore whether these effects occur when the charity’s cause is not aligned with a person’s moral profile;(iii)to examine whether the effects of (in)congruent calls-to-action are moderated by participants’ moral internalization scores;(iv)to investigate whether attitudes toward CB mediate the effect of (in)congruent calls-to-action on CB and whether descriptive social norms mediate the effect of normative information on CB;(v)to investigate whether individuals’ moral foundations can be predicted based on their Facebook behavior.

In previous studies, calls-to-action congruent with one’s moral foundations increased CB (Winterich et al., 2012). Therefore, we hypothesize that morally congruent calls-to-action will have a greater positive impact on CB compared with morally incongruent and neutral calls-to-action, regardless of whether the charity cause itself is in line with one’s moral foundations. Furthermore, we hypothesize that providing participants with normative information, thus making the descriptive norm salient, will significantly affect CB. Additionally, we expect that the impact of morally congruent calls-to-action will be greater in individuals with high moral internalization compared to individuals with low moral internalization. Also, in line with the assumptions of TPB (Ajzen, 1985, 1991), we expect that the effects of calls-to-action congruence on CB will be mediated by attitudes toward CB, and that the effect of normative information on CB will be mediated by the perception of descriptive social norms. Finally, although this part of the research would be purely exploratory, we expect to be able to predict some of the participants’ moral foundations by his/her Facebook behavior. The proposed effects are shown in the Figure 1.

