### The Independent Variables

#### Moral Foundations

Participants’ moral foundations will be assessed using the latest version of the MFQ (Graham et al., 2008; see http://www.moralfoundations.org for more information and to access the questionnaire). The questionnaire comprises 30 items, asking participants about the extent to which different factors are relevant in their moral decision-making. Each of the five foundations is assessed with six items, and the participants’ task is to evaluate the relevance of an item or agreement with the item on a six-point scale (0 = not at all relevant/strongly disagree; to 5 = extremely relevant/strongly agree). To obtain the final score on each of the subscales, the evaluations are summed up and consecutively divided by the number of items related to the particular subscale. A score between 0 and 5 will be calculated for each of the moral foundations subscales. The internal consistencies of the subscales were reported to be α = 0.69 (Harm), α = 0.65 (Fairness), α = 0.71 (Ingroup), α = 0.74 (Authority) and α = 0.84 (Purity) (Graham et al., 2011). The MFQ is open-access and freely accessible for research purposes.

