## Statistical Analysis

To test for the effects of moral congruence of the calls-to-action, descriptive social norms, and their interaction on donations of time and money, a multivariate analysis of variance (MANOVA) will be conducted. In the same analysis, a test for the moderating effect of moral internalization on the congruence of the calls-to-action will also be conducted. This approach allows researchers to account for potential relationships between our dependent variables, and to test whether the experimental manipulations influence participants on a combination of different types of donations (Field, 2009). Furthermore, in comparison with univariate ANOVA, that requires several individual tests, using MANOVA reduces the probability of making a *Type I* error.

To test whether attitudes toward CB mediate the effects of (in)congruence of the calls-to-action on CB, and whether descriptive social norms mediate the effects of normative information on CB, a mediation analysis will be conducted. This can be done by using the bootstrapping method developed by Preacher and Hayes (Hayes, 2013). This is because previous approaches related to this analysis, such as the causal step approach (Baron and Kenny, 1986), have been criticized for lack of power, the underlying assumptions and inability to directly evaluate potential mediation (MacKinnon et al., 2002).

To determine if people’s moral foundations can be predicted from their Facebook data, various machine learning algorithms can be employed^5^. However, as this part of the study is exploratory and primarily concerned with maximizing prediction accuracy, we cannot specify the exact algorithm which will be reported. Various models and approaches can be tried out, choosing the one that exhibits the least amount of generalization error, i.e., the one that performs best on unseen data, which will be determined through cross-validation. Some possible approaches are LASSO (*Least Absolute Shrinkage and Selection Operator*) regression, multiple linear regression on clustered data and principal component regression^6^ (James et al., 2013; Kosinski et al., 2016).

The analyses can be conducted using the R language (R Core Team, 2017). For implementing the various machine learning algorithms, we will use existing packages, such as glmnet (Friedman et al., 2010), irlba (Baglama et al., 2017) and topicmodels (Grün and Hornik, 2011).

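### Facebook prediction (exploratory aim v): the cross-validation error that picks the model is the only accuracy estimate named, and it is optimistic once used for picking

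*Protocol article*

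**What the plan says.** Under Statistical Analysis, the paragraph on Facebook data gives its purpose as finding out whether moral foundations are predictable. It states that "we cannot specify the exact algorithm which will be reported" and that "Various models and approaches can be tried out". The choice falls on the model that "exhibits the least amount of generalization error, i.e., the one that performs best on unseen data, which will be determined through cross-validation". LASSO is offered as one example, alongside "multiple linear regression on clustered data and principal component regression". The list is illustrative and sets no limit on the number of models or tuning values.

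Aim (v), under Aims and Hypotheses, asks whether foundations "can be predicted based on their Facebook behavior". The same section calls this part purely exploratory and adds that "we expect to be able to predict some of the participants’ moral foundations by his/her Facebook behavior". There are five outcomes: "A score between 0 and 5 will be calculated for each of the moral foundations subscales" (Moral Foundations).

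The paragraph does not say which accuracy figure will accompany the chosen model. It neither mentions nor rules out a hold-out sample or nested cross-validation.

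**The concern.** Cross-validation estimates unseen-data performance for a procedure fixed before the scores are seen. Here the scores decide the procedure. Each candidate's score is its true performance plus noise, and taking the best of many favours candidates whose noise was lucky. The winning score is then no longer an unseen-data estimate, although the text equates the two.

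This matters because aim (v) is close to a yes/no question about whether any predictive signal exists. Near zero signal, a small upward bias can change the apparent answer. The Abstract says that charities could use successful prediction to find and target likely supporters, and the introduction adds avoiding people unlikely to support a cause. A misleading positive would feed into that use.

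**Working it through.** **The plan's own figure.** The article gives no figure for the Facebook part. The only sample size stated is for the confirmatory MANOVA: 439 at 90% power and 344 at 80%, for f² = 0.02 and α = 0.05 (Participants). Both reproduce exactly from the noncentral F distribution for Pillai's trace with p = 2 responses and k = 3 effect degrees of freedom: s = min(p, k) = 2, df1 = pk = 6, and noncentrality N·s·f² = 439 × 2 × 0.02 = 17.56 at N = 439. Adding 20% gives 439 × 1.2 = 526.8, or 527. These numbers serve below only as plausible upper values for n. Participants may refuse Facebook access (Stepwise Procedure), so n = 200 is also shown.

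**Simulation with no signal.** All of the following are assumptions, not plan values:
- 300 sparse binary likes and one outcome independent of them.
- 10-fold cross-validation.
- Either 16 candidates (principal component regression at 6 sizes, regression on clustered likes at 4 sizes, LASSO at 6 penalties; 6 + 4 + 6 = 16) or 3 candidates (one fixed version of each).
- The winner is refitted and scored on 1,000 new subjects.

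R² = 1 − Σ(y − prediction)² / Σ(y − training mean)². The gap is the winner's cross-validated (CV) R² minus the same model's R² on new subjects.

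| n | Candidates | Runs | Winner's CV R², mean | 95th percentile | CV R² above 0 | New-data R² | Gap |
|---|---|---|---|---|---|---|---|
| 439 | 16 | 250 | 0.0055 | 0.0218 | 68% | −0.0088 | 0.0143 |
| 439 | 3 | 250 | −0.0005 | 0.0134 | 37% | −0.0050 | 0.0045 |
| 527 | 16 | 150 | 0.0044 | 0.0188 | 64% | −0.0075 | 0.0119 |
| 527 | 3 | 150 | 0.0000 | 0.0080 | 31% | −0.0024 | 0.0024 |
| 200 | 16 | 150 | 0.0120 | 0.0572 | 61% | −0.0223 | 0.0343 |
| 200 | 3 | 150 | −0.0156 | 0.0437 | 25% | −0.0353 | 0.0197 |

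The simulation error on the 68% is about √(0.68 × 0.32 / 250) = 0.03. For comparison, in a separate no-signal simulation at n = 439, a single one-component model fixed in advance had CV R² above zero in 16% of cases.

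**If the winner is chosen by correlation instead.** The nominal one-sided 5% cut-off is 1.645/√n, which is 0.079 at n = 439.
- 16 candidates, n = 439: mean CV r 0.071 (95th percentile 0.155), above the cut-off in 43% of runs; r on new subjects −0.001.
- 16 candidates, n = 527: mean 0.061, above the cut-off in 37%. At n = 200: mean 0.108, above it in 42%.
- 3 candidates, n = 439: mean 0.029, above the cut-off in 18%.

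This applies only when correlation is the selection criterion. In the separate simulation at n = 439, the correlation of the model chosen by lowest error averaged −0.012.

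**With the remedy.** Scoring the winner on data not used to choose it gives mean R² of −0.009 and mean r of 0.00 (n = 439, 16 candidates), so the upward bias disappears.

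**The case against.** The strongest objection is that the text ties cross-validation only to choosing a model. A reader might infer that the same score will be published as the accuracy. The article does not say so: what it describes as reported is the algorithm, and resampling detail is something a condensed article may leave to a fuller plan. Two footnotes to the paragraph were also not available in the text reviewed. This part stands, and the point is worded accordingly.

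A reader might also infer that the rule yields a positive finding from pure noise. The documents do not support that either, because they give no threshold, test or other criterion for declaring success.

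Nor do they set a best-of-five rule. Hoping to predict some foundations is an expectation, not a plan to report only the best. The separate simulation (60 runs, n = 439) found that the best of five outcomes, chosen by correlation, passed the nominal cut-off in 93% of no-signal datasets. It treated the five scores as independent, whereas the article groups the foundations into two families, so that figure may overstate the risk.

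Finally, the plan selects on error, where the bias is small, and the work is optional, exploratory and separate from the confirmatory part (Limitations).

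What remains is narrower. The only performance estimate named is the one that makes the selection, and it is described as performance on unseen data. Followed as written, the paragraph produces no accuracy figure free of selection. Exploratory status justifies free choice of algorithm but does not correct that description.

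**Conclusion.** The point holds as a modest, easily corrected weakness in the exploratory part. If the selection score is used to answer aim (v), it is optimistic by about 0.012 to 0.034 in R² with 16 candidates, the larger value at n = 200. With three fixed candidates the gap is below 0.005 at n = 439 or 527. At n = 200 it is about 0.020, but the average score stays below zero. The 16-candidate case needs nothing beyond the three example approaches with a few tuning values each.

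The practical risk is a claim of weak prediction, not of strong prediction. It is greatest when many models are tried, when few participants share data, or when a correlation is set against a nominal cut-off. The sizes rest on assumed numbers of likes, models and participants sharing data; the direction of the bias does not. The MANOVA, the mediation analyses and the sample size are untouched.

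**What to change.** Keep the free choice of algorithm and add a sentence such as: model selection and all tuning will be done in the inner loop of nested cross-validation, and the reported accuracy will come from the outer loop, for all five foundations, with intervals. The candidate list should be closed before outer-loop results are seen; otherwise the outer loop becomes a selection step too. An alternative is a random hold-out, locked until the final model is fixed and opened once.

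Reporting all five foundations also deals with any selective emphasis on the best one. A permutation test adjusted for five outcomes is an optional addition and not needed to correct the problem.

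Nested cross-validation costs only computing time. A hold-out leaves a smaller training set, which matters more if few participants share their data. Nothing in the confirmatory part has to change.

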## Impact and Limitations

### Anticipated Results

Based on the theory and the literature reviewed in the introductory part, we can make some educated expectations regarding our results. First, in line with previous research (e.g., Winterich et al., 2012; Kidwell et al., 2013; Nilsson et al., 2016), we expect that our intervention in terms of morally (in)congruent calls-to-action will have a significant impact on CB. Specifically, we expect that morally congruent appeals, regardless of whether they are individualizing or binding, will foster significantly more CB compared to incongruent or neutral appeals.

Regarding the social norms, we expect that making the descriptive norms salient (“*most of the participants donate*”) will influence one’s subsequent CB. Although some of the previous studies did not find an effect of descriptive norms on CB (e.g., Smith and McSweeney, 2007; van der Linden, 2011), it seems that these studies failed to make the descriptive norms salient enough, which seems to be a prerequisite for them to be effective in influencing behavior (Cialdini et al., 1990). Thus, we hypothesize that participants who receive descriptive norms in their appeal will donate more of their money and time compared to those who do not receive a descriptive norm.

Since we expect both morally (in)congruent calls-to-action and descriptive social norms to have an effect on CB, we hypothesize that participants receiving a morally congruent call-to-action with a descriptive norm will donate the most. Furthermore, based on previous findings regarding the influence of moral identity internalization on CB (e.g., Winterich et al., 2012), we expect to find a significant two-way interaction effect of morally (in)congruent appeals and moral identity internalization on CB. A larger effect of morally (in)congruent appeals on CB is expected for those who are high on moral identity internalization as compared to those who are low on moral identity internalization (see Figure 3).

**FIGURE 3 F3:**
[figure not shown]
The expected effects of morally (in)congruent calls-to-action and descriptive norms on different levels of moral identity internalization.

We also expect to find mediating effects of attitudes and descriptive norms on the relationship between (in)congruent calls-to-action and normative messages on the one side and CB on the other. More precisely, we expect that the individualizing/binding calls-to-action will have a positive impact on donation attitudes of those participants who are high on individualizing/binding moral foundations, resulting in their willingness to donate more of their time and money. Since our second charity cause (refugee support) is already supposed to be more appealing for those high on individualizing foundations, we do not expect the individualizing calls-to-action to have a major additional impact on participants’ donating attitudes or behavior. On the other hand, we do expect that the binding calls-to-action will have a bigger impact, shifting the attitudes and increasing CB of those higher on binding moral foundations, since they are expected to have relatively negative attitudes toward such charity. See Figure 4 for a schematic representation of these effects.

**FIGURE 4 F4:**
[figure not shown]
The expected effects of individualizing, neutral and binding calls-to-action on donating attitudes and CB, with respect to participants’ scores on MFQ.

### Significance of Research

We believe that the current project makes an important contribution both in theoretical and in practical terms. In theoretical terms, we hope to expand the knowledge about the scope of morally (in)congruent appeals. Rare previous research did examine the effects of the congruence between both the appeals and individual’s morality, as well as charity causes and individual’s morality. However, within the current project, we plan to explicitly contrast these two. We aim to explore whether the appeals tailored in line with one’s morality can enhance one’s donations to charitable causes, even in the case of charities for which there is no original affinity. This way, we contribute to the theoretical considerations of the role of morality in CB, but also sketch potential fundraising strategies for charities with different causes. Furthermore, another significant theoretical contribution of this project is the investigation of the role of attitudes in CB change. Specifically, within this project we not only want to show that congruent calls-to-action can have a positive impact on CB, but also to elucidate the mechanism through which this effect operates (i.e., by affecting attitudes toward CB).

Besides the effect of congruent appeals on attitudes and CB, within this project we will investigate the role of descriptive social norms in CB. Specifically, we want to test potential boundary conditions for the effectiveness of descriptive norms, especially related to their saliency. However, here we also want to go a step further and show that, if salient normative information indeed can affect CB, it probably does so through changing one’s perceptions about descriptive norms related to CB. Therefore, we believe that the current project contributes to the theoretical knowledge in several important ways.

More importantly, however, we hope that the project will have useful practical implications. Specifically, we hope to be able to provide charities with some simple yet effective tools that they could utilize in subsequent fundraising campaigns. For example, charities will be able to benefit from the often easily attainable knowledge about the approximate ideological positions of their target group by changing the way in which they deliver information about their causes and frame donation pitches. In this way, they could decrease the risk of turning away people who would potentially become their donors, by addressing them the right way. Given the low implementation costs of these interventions, we believe that charities can significantly benefit from them even if the effect sizes are modest.

Looking at the previous literature, we can expect to find small to medium effect sizes of our interventions on donating behavior. For example, Winterich et al. (2012) found small to medium effect sizes for both charitable intentions and donations (Cohen’s *d* between 0.28 and 0.46). Croson et al. (2009) found a medium impact of descriptive social norms on donations to public radio’s (Cohen’s *d* = 0.58). However, we believe that, from the perspective of charity donations, even modest effects can have big practical importance. Statistically speaking, even if our interventions exhibit only small effects on CB (Cohen’s *d* = 0.2), this still means that 58% of donations from people from the *congruent appeal + norm* intervention will be higher than the mean donation from people from the *no intervention* condition. In case we find medium effects (*d* = 0.5), as much as 69% of the *intervention* donations will be higher than the mean of the *no intervention* donations (see http://rpsychologist.com/d3/cohend/ for the visualization and interpretation of Cohen’s *d* effect sizes). Thus, taking into account the relative ease and low cost of the implementation of these interventions, we believe that any kind of improvement in terms of donations can be considered as practically significant for charity organizations.

### Limitations

Despite the potential benefits, the present project is not without limitations. Specifically, the hypothetical bias is one potential problem that is well known in the literature. Hypothetical bias is the difference between the stated and revealed value of a certain good (Murphy et al., 2005). In terms of charitable giving, people often state they are willing to donate significantly more money than they would really donate. One reason for this could be related to loss aversion which is more pronounced in case of giving real money than hypothetical money. Although we acknowledge that this is a problem, we believe that our approach at least attenuates it. Specifically, in line with the findings of Murphy et al. (2005) meta-analysis, stating that choice-based elicitation could be important in reducing the bias, we are giving our participants the choice between several different ways of allocating the 50$ Amazon card. Furthermore, we are providing real, valid gift cards from which at least some of the participants will actually donate money. Although this is still far from representing a real situation in which people are giving away their own money, we believe that it is a step away from a purely hypothetical situation in which no money would be donated. In their meta-analysis, Murphy et al. (2005) found that the median hypothetical bias fell between 1 and 1.5 (i.e., in hypothetical situations people donated between 1 and 1.5 times more than in real situations). Although impossible to know, we hope that with this approach the hypothetical bias in studies based on this protocol would not be much higher than this estimation.

However, it is important to note that, although loss aversion and hypothetical bias should affect the amount people would be willing to donate in absolute terms, it should not affect the relative differences among groups within the study. Specifically, as the participants will be randomly selected into different groups, we have no basis to believe that some groups will have significantly different hypothetical bias from others. Therefore, although absolute amounts would certainly be inflated, we believe that loss aversion and hypothetical bias should not play a significant role in our study, as the relative differences between the groups will still be observable.

A second limitation of the current study is grouping. Although we can expect the majority of our participants to fit into one of the two categories – those who rely more and those who rely less on binding foundations – some participants will not fit into this binary classification. For example, Iyer et al. (2012) showed that libertarians’ pattern of moral foundations significantly differs from those of liberals and conservatives. This means that our (in)congruent calls-to-action will not be adequately tailored toward these participants, and this may impact the overall effectiveness of our manipulations. However, most participants are expected to fit into our two categories, and those who do not will be randomly distributed between conditions. Future studies could benefit from constructing a wider range of calls-to-action to cover different types of moral foundation profiles.

Finally, we would like to address what we see as probably the most significant problem with following this protocol, and that is the Facebook app. Namely, not all researchers will be in a position to collect the data with a custom made app in order to gain access to participants’ Facebook data. However, we already noted that the part of the protocol regarding accessing Facebook data and predicting moral foundations from it is purely exploratory, and independent of the former, confirmatory part. In other words, one can reconstruct all the steps included in the confirmatory part of the protocol (i.e., presentations of the questionnaires, calls-to-action, attitudes and norms measures and dependent variables of donating time and money) using only readily available online survey tools. We believe that such a study would be easily implemented, interesting and beneficial on its own.

